##### PrEPTECH Acceptability and Feasibility

The acceptability and feasibility of PrEPTECH as a telehealth HIV PrEP care intervention for young cisgender men and transgender women who have sex with men will be assessed through multiple measures, including the likelihood of recommending PrEPTECH; preference for continuing PrEPTECH beyond the study; and other variables assessing the perceived trustworthiness, privacy, helpfulness, and convenience of and comfort with PrEPTECH. We will also calculate a mean System Usability Scale score, which is a standard scale for evaluating web apps [45], and conduct a thematic analysis of responses to 4 free-text questions about participants’ perception of and experience with the PrEPTECH intervention and barriers to PrEP access encountered during the study. We will also examine clinical data, data on study attrition and completion, and other data from study implementation records.

##### Demographics

Participants’ age, sex, gender, gender identity, sex partners’ gender, sexual orientation, race, ethnicity, educational attainment, and living situation (living alone or with housemates or family) and whether languages other than English are spoken at participants’ home will be assessed.

##### Moderators and Mediators

The following parameters will be assessed at baseline as potential moderators of PrEP uptake: history of PrEP use, HIV risk perception (assessed using the Perceived Risk of HIV Scale) [46], PrEP attitudes (assessed using a PrEP attitude and stigma scale with scores ranging from 10 to 50) [47], behaviors associated with HIV risk (eg, instances of anal intercourse without a condom in the past 90 days), health insurance status, and reasons for enrolling in the study (using a predefined list of possible reasons formulated by the study staff with input from the CAB). A series of questions assess the barriers to PrEP access participants may have encountered during the study period as a potential mediator of differences in PrEP uptake. Participants are asked to attest to whether they have encountered specific PrEP access barriers compiled in consultation with the CAB and with reference to the literature falling into the categories of financial or insurance coverage, health care access, medical concerns, privacy, PrEP stigma, and practical considerations (including loss, theft or selling of medication). A single item on the 2 follow-up surveys will also ask all participants to rate whether they have a source of PrEP that meets their needs.

### Data Analysis

#### Overview

We will report the participant flow through the trial and the results in line with the CONSORT (Consolidated Standards of Reporting Trials) guidelines [48]. All analyses will be carried out following intention-to-treat principles. Data from participants will be allocated to the arm they were initially assigned to, regardless of whether they complete the intervention.

Data analysis will be conducted in SPSS (version 29 or higher; IBM Corp). Descriptive statistics will be calculated to describe the sample at baseline. Binary and categorical variables will be assessed through counts and percentages, and continuous variables will be assessed through means and SDs (medians will be computed for highly skewed variables). To assess baseline equivalence between the intervention and control arms of the study, regression analyses will be performed using age, race, ethnicity, gender, and educational attainment as dependent variables, with intervention condition as the independent variable. The groups will be considered not equivalent at baseline if a given variable differs significantly (*P*<.05) between the intervention arms. Differential and overall attrition will also be assessed using the What Works Clearinghouse recommended approach [49]. We expect ≤5% of the data to be missing; therefore, a complete case analysis is planned with no outcome or baseline imputation. However, if missing data go beyond 5%, then multiple imputation will be explored and run using the *mice package* in R (R Foundation for Statistical Computing) [50].

#### Primary and Secondary Outcome Analyses

##### Objective 1

To assess the effectiveness of PrEPTECH in enhancing PrEP uptake in comparison with the control condition, multiple logistic regression will be applied with the primary outcome (taking at least one dose of PrEP in the last 90 days, a dichotomous variable) as the dependent variable. The model will also include indicator variables denoting (1) the intervention group, (2) the number of days between the baseline and follow-up surveys (if there is a large range, which we do not expect), (3) the standard demographics of age at baseline and race and ethnicity at baseline, and (4) a set of a priori demographics and outcome-related covariates that screened positively as candidates for inclusion. A priori covariates that will be screened as candidates for inclusion into the model include gender, educational attainment, health insurance status, state, location, language spoken at home, sexual orientation, gender of sex partners, sexual risk factors, and the participants’ relationships with the persons they are living with. If there is high correlation (*r*>0.50) between some of these indicators, they will be excluded from the model. Bivariate analyses will be used to test for relationships between the outcome variable and potential covariates, with a threshold of *P*<.15. The standardized effect size of the intervention on PrEP uptake will also be calculated to determine the magnitude of the effect of the intervention.

##### Objective 2

To evaluate the acceptability of PrEPTECH as a telehealth HIV PrEP care intervention for young cisgender men and transgender women who have sex with men, we will assess participants’ likelihood of recommending PrEPTECH; participants’ preference for continuing PrEPTECH beyond the study; and other variables assessing the perceived trustworthiness, privacy, helpfulness, and convenience of and comfort with PrEPTECH among those in the intervention group. The percentage of participants expressing agreement or strong agreement with each item will be calculated. The System Usability Scale score will be calculated according to published guidelines to obtain a score out of 100 [45]. In addition, free-text answers to 3 questions about the benefits and drawbacks of PrEPTECH and how participants would characterize the intervention to a friend will be analyzed using a thematic approach.

The feasibility of PrEPTECH as a telehealth HIV PrEP care intervention for young cisgender men and transgender women who have sex with men will be assessed through a review of the study records. Clinical data will be used to assess loss to follow-up at various intermediate points in the intervention (eg, failure to return at-home laboratory kits or complete asynchronous medical intake forms). Records of clinical communications, written prescriptions, and efforts to assist intervention arm participants and to remind them to complete intervention steps will also be reviewed, with the number of contacts required at various stages calculated.

##### Objective 3

To examine the effects of PrEPTECH on adherence to PrEP, we will examine continuous measures. In each case, a multiple linear regression model will be applied. As described under *Objective 1*, the model will include (1) the intervention group, (2) the number of days between the baseline and follow-up surveys (if applicable), (3) the standard demographics of age at baseline and race and ethnicity at baseline, and (4) a priori demographics and outcome-related covariates that screened positively as candidates for inclusion. Variables will be screened in as described earlier.

The standardized effect size of the intervention on PrEP adherence will also be calculated to determine the magnitude of the effect of the intervention.

##### Objective 4

To examine the moderators of PrEP use, including HIV risk perception, PrEP attitudes, indications of sexual risk, insurance status, and reason for enrolling in the study, we will create multiple logistic regression models with PrEP uptake at 3 and 6 months as the outcome variable, intervention group as the predictor, and the potential moderator as an interaction term. The moderator will be considered statistically significant if *P*<.05.

A more detailed statistical analysis plan will be agreed upon before final analysis.

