### Sample Size

We calculated the sample size to provide adequate statistical power for our first objective, which is to test the effectiveness of a telehealth intervention, PrEPTECH, in enhancing PrEP uptake. Data suggest that PrEP uptake among relevant populations is low. Only 16% of young people aged 16 to 24 years use PrEP [6]. We also reviewed recent RCTs aimed at increasing PrEP uptake in comparable study populations. A pilot study of linkage to PrEP care among men who have sex with men and transgender women identified as partners of people diagnosed with a sexually transmitted infection (STI) found an uptake rate of PrEP of 11% among controls receiving standard HIV prevention programming, including PrEP care [31]. In a pilot trial of a 2-session motivational interviewing–based behavioral intervention, 28% of controls receiving treatment as usual at an urban STI clinic received a PrEP prescription [35]. Furthermore, 2 RCTs of web-based interventions for increasing PrEP uptake among sexual minorities with published protocols estimated anticipated control arm uptake ranging from 2% to 15% for the purpose of their power analyses [36,37].

Using this recent research on PrEP uptake in relevant populations and comparable research projects, including ongoing RCTs of digital interventions, we assumed 20% PrEP uptake in the control population. We proposed a minimum sample size target of 192 participants. Retaining 83.3% (160/192) of these participants at the 90-day and 180-day follow-up was our benchmark, as a loss to follow-up of greater than 20% in RCTs is seen as potentially introducing a source of bias [38]. We calculated statistical power using the following assumptions: power (1 – β)=.80, significance level (α)=.05, PrEP uptake in the control group of 20%, and PrEP uptake in the intervention group of ≥40%. The power analysis results indicate a required sample size target of 96 per group or 80 per group after anticipated attrition.

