### Intervention

Participants allocated to the intervention arm of the study gained access to a web-based telehealth platform called PrEPTECH, which provides PrEP education via self-guided reading material, access to laboratory testing for PrEP eligibility delivered to a participant’s home, and optional SMS text messages or email reminders to aid in medication adherence. PrEPTECH also provides access to telehealth care and PrEP prescriptions for eligible patients asynchronously through a web-based form or synchronously through telephone appointments with the study clinician, an infectious disease physician with expertise in PrEP care licensed in California and Florida. The PrEPTECH intervention tested here is an extension of the piloted PrEPTECH intervention. A brief report on the results of the pilot also discusses the development of the initial intervention by a multidisciplinary team in concert with a previous CAB [42]. It was adjusted to serve a larger group and to be completely web-based. In the second version of PrEPTECH, we incorporated a home laboratory testing kit service, built a platform for offering web-based health evaluations, and developed back-end systems for PrEPTECH to enable the clinical team to review submitted information and communicate with participants. The site was also redesigned for mobile platform compatibility.

All participants who completed at-home laboratory testing and an asynchronous or telephone appointment with the study clinician for whom PrEP was indicated received a prescription for Truvada (emtricitabine, 200 mg or tenofovir disoproxil fumarate, 300 mg). Adult cisgender male participants aged 18 to 27 years received a free 30-day supply of PrEP and subsequently had to pay for PrEP medication through insurance, through patient assistance programs, or out of pocket, should they choose to continue taking PrEP. Adolescent cisgender male participants aged 15 to 17 years and adult transgender female participants aged 18 to 27 years received free PrEP medication for the duration of their 6-month participation in the study because these subgroups were not included in the pilot study of PrEPTECH. Knowing less about the suitability of this intervention for these susceptible populations, the study team opted to provide free medication to them for the duration of the study. PrEPTECH also provides support for signing up for PrEP access programs, prescription transfer, and coordination with community partners.

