### Participant Timeline

The entire 6-month web-based study is completed on the PrEPTECH website. A sequential illustration of participants’ experiences is shown in Figure 1.

Recruited prospective participants review web-based materials on the PrEPTECH website and elect whether to create a web account, which requires them to verify their email address and phone number and provide their name.After creating an account, prospective participants are screened for eligibility via a web-based survey. Those meeting the inclusion criteria proceed to step 3.Each participant then verifies their identity by providing a photo of themselves with a photo ID card or a link to a public social media profile that shows their name with a visible photo of themselves.Participants who provide identity verification are invited to complete the baseline web-based survey.Each participant is randomized after baseline completion, informed of their assignment, and provided with standardized web-based resources on PrEP access or brought to the first step of the PrEPTECH intervention.All participants are invited to take the midpoint survey 90 days after the baseline survey.All participants are invited to take the final survey 180 days after the baseline survey.

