### Outcomes

#### Primary Outcomes

PrEP initiation at 3 months after enrollment will be assessed using participant self-report of having taken at least one dose of PrEP medication between study enrollment and midpoint survey administration.

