#### Secondary Outcomes

##### PrEP Initiation

PrEP initiation at 6 months after enrollment will be assessed using participant self-report of having taken at least one dose of PrEP medication at any point during the intervention period.

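### The single primary outcome is stated with two recall windows that agree only for a midpoint survey answered on day 90, and survey delay enters the primary model conditionally on the data

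*Protocol article*

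**What the plan says.** Under Outcomes, Primary Outcomes, initiation at 3 months is scored from self-report of "having taken at least one dose of PrEP medication between study enrollment and midpoint survey administration". Under Primary and Secondary Outcome Analyses, Objective 1, the dependent variable of the logistic regression is labelled the primary outcome and described as "taking at least one dose of PrEP in the last 90 days, a dichotomous variable".

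The Participant Timeline sets the schedule: "All participants are invited to take the midpoint survey 90 days after the baseline survey". Data Collection and Management adds automated reminders and customized follow-up. The article states no closing date for the midpoint survey. The timeline also says "Each participant is randomized after baseline completion", so the time a participant takes to answer the midpoint survey is always observed after allocation.

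The Objective 1 model includes "the number of days between the baseline and follow-up surveys (if there is a large range, which we do not expect"). It does not say what range counts as large.

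For comparison, the secondary outcome of initiation at 6 months is scored from "having taken at least one dose of PrEP medication at any point during the intervention period", which is not a 90-day look-back.

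**The concern.** The trial has one primary outcome, and two sections give different rules for scoring it. A programmer following the outcome definition and one following the analysis section could code the same late responder differently. Nothing in the article says which text governs.

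The participants who could be rescored are those who started, stopped early and answered late. That pattern is at least plausible in the intervention arm, where "Adult cisgender male participants aged 18 to 27 years received a free 30-day supply of PrEP" and then had to arrange payment to continue. Any rescoring might therefore not be equal between arms.

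The survey-delay covariate raises a related problem. Whether it enters the primary model depends on a look at the data against no stated threshold, and it is a post-randomization variable. If delay is influenced by arm, adjusting for it can distort the comparison. It also cannot correct an outcome coded on the wrong window. A large range of delay is the very situation in which the two windows diverge.

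**Working it through.** **1. The plan's own figure.** Sample Size gives "power (1 – β)=.80, significance level (α)=.05, PrEP uptake in the control group of 20"%, intervention uptake of at least 40%, and 80 per group analyzed (96 enrolled). The pooled-variance formula, two-sided, is

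n = [1.960·√(2·p̄(1−p̄)) + 0.842·√(p₀(1−p₀)+p₁(1−p₁))]² / (p₁−p₀)²

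With p₀ = 0.20, p₁ = 0.40 and p̄ = 0.30, n = 82 per group after rounding up. The unpooled form gives 79 and the arcsine form about 80. With retention of 160/192, 80/0.8333 = 96. The stated size reproduces, and this point does not dispute it. Power at 80 per group is 0.79.

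**2. The two windows.** Take enrollment and baseline as day 0, and let T be the day the midpoint survey is answered.

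| Text | Window |
|---|---|
| Primary Outcomes | day 0 to day T |
| Objective 1 | day T−90 to day T |

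At T = 90 they are identical. For T > 90 they differ by the days before T−90. If L is the day of the last dose, the score changes only when L < T−90. Anyone who never started, or who took any dose in the 90 days before answering, scores the same under both texts.

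**3. How late is late enough.** Take a 30-dose daily course that is not continued, so that L = s + 29 with first dose on day s. The values of s are assumptions; the article gives none. The score changes when T > s + 119.

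| First dose, day s | Last dose, day L | Rescored if survey answered after day |
|---|---|---|
| 7 | 36 | 126 |
| 14 | 43 | 133 |
| 21 | 50 | 140 |
| 30 | 59 | 149 |

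In these examples the survey has to be more than 36 to 59 days late. Someone who took a single dose and stopped would be rescored sooner: with that dose on day 14, after day 104.

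**4. Illustrative effect on power.** Let f be the share of initiators whose doses all precede the look-back. It is assumed, because the article gives no basis for it. Power is at 80 per group, two-sided 0.05, starting from 40% against 20%.

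| f | Only intervention initiators rescored | Same share rescored in both arms |
|---|---|---|
| 0 | 0.79 | 0.79 |
| 2% | 0.76 | 0.78 |
| 5% | 0.71 | 0.76 |
| 10% | 0.62 | 0.73 |

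For example, f = 5% in the intervention arm alone means 0.40 × 0.95 = 0.38 against 0.20.

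**5. The 6-month outcome.** The look-back phrase is attached to the primary outcome only. If it were carried into a 6-month model, it would conflict with the secondary definition, which counts a dose at any time in the intervention period.

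**The case against.** The strongest reply is that this is loose wording. The Primary Outcomes section is the definition, and the Objective 1 phrase is a parenthetical gloss. The article uses 90 days as shorthand for the interval from enrollment to the midpoint survey throughout, the survey is issued on day 90, a large range is not expected, and a more detailed analysis plan is promised. Few people could change score: they must have stopped PrEP early and, after a 30-dose course, also have answered about six weeks late, despite reminders and a US $50 payment. Education, a mailed kit, results, clinician review and mail delivery all come before a first dose, which pushes the threshold later. The intervention also offers a 6-month prescription and payment support, and two subgroups had free medication throughout. Most of this stands, and it limits the size of the problem. It does not remove the contradiction, because the analysis section is the text from which the outcome would be coded.

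A reader might infer a material loss of power. Losing 2 to 5 points from a 40% intervention rate would give 71% (38 v 20) or 57% (35 v 20) at 80 per arm. The documents do not support that reading. It needs 5% to 12.5% of intervention initiators to be both early stoppers and very late responders, with the control arm untouched, and no delay data are given. In addition, 229 were recruited. At the planned retention that is about 229 × 0.833 / 2 ≈ 95 per arm, where power for 40 v 20 is about 86%.

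A reader might also infer that adjusting for delay does bias the result. Survey reminders and payments go to all participants, and nothing in the article shows that delay differs by arm. Intervention participants do have extra contacts around day 90 (second kit, third intake form), so an arm effect on delay is possible but not shown.

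**Conclusion.** The point holds as an inconsistency in the only primary outcome, of minor to moderate severity. The two windows coincide for a survey answered on day 90 and can score early stoppers differently after that. How many participants are affected cannot be derived from the article and may be near zero. The power figures rest on an assumed share f and show direction only. The planned sample size is unaffected.

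The conditional delay covariate is a weakness as written: its entry depends on an undefined look at the data, and it is observed after randomization. The documents support that statement, but not a claim that the arm comparison is in fact biased.

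**What to change.** Before outcomes by arm are examined:

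- Replace the look-back phrase in Objective 1 with the definition under Primary Outcomes: at least one dose since enrollment, as reported at the midpoint survey.
- Remove days between surveys from the primary model.
- Add one sensitivity analysis that either adjusts for delay or restricts to surveys answered within a pre-stated window. The choice and the width of the window are for the sponsor.
- Do not carry the 90-day look-back into the 6-month initiation model.

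This does not depend on first-dose dates, which the article does not describe as collected, and it does not set observed late answers to missing. Data collection has ended, so the choice and its date should be documented.

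The cost is a change of wording and one extra analysis. For late responders the window runs past day 90, so a few first doses after that day could count as initiation at 3 months; the sensitivity analysis addresses this.

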Eligible participants were randomized equally between the intervention arm, a web-based telehealth program offering a fully web-based pathway to PrEP, and the control arm, a dynamic web page containing publicly available informational resources about PrEP. We intended to ensure equal allocation of participants across the 4 study areas and equal numbers of adolescent cisgender males and adult transgender females in each study arm (approximately 20 individuals belonging to each subgroup in each study condition).

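### Most covariates in the primary model are chosen by testing them against the trial outcome, under a correlation rule that could drop geography and a candidate list that omits prior PrEP use

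*Protocol article*

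**What the plan says.** The Objective 1 analysis is a multiple logistic regression of PrEP uptake. Besides arm, it always contains "the standard demographics of age at baseline and race and ethnicity at baseline". Days between surveys is added if its range is large. The rest of the model is "a set of a priori demographics and outcome-related covariates that screened positively as candidates for inclusion".

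Ten candidates are named: gender, education, insurance, state, location, home language, sexual orientation, gender of sex partners, sexual risk factors, and relationship to the people the participant lives with. The selection rule is "Bivariate analyses will be used to test for relationships between the outcome variable and potential covariates", at P<.15. For high correlation (r>0.50), the text adds "between some of these indicators, they will be excluded from the model". Objective 3 uses the same screening.

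Three other sections bear on this:
- Recruitment and Randomization: "We intended to ensure equal allocation of participants across the 4 study areas". The same sentence also aims to match the two arms on how many adolescents and transgender women they contain.
- Moderators and Mediators: the baseline survey covers "potential moderators of PrEP uptake: history of PrEP use, HIV risk perception" and other factors.
- Eligibility Criteria: PrEP use excludes a person only if it fell in the past 30 days.

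**The concern.** Naming candidates in advance does not pre-specify the model when the outcome decides which of them enter. An adjusted odds ratio is conditional on its covariates, so the estimated quantity itself is not settled until outcomes have been examined.

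The correlation rule adds a second problem. State and location are both candidates, and the areas are nested in states (two in California, two in Florida). The overlap is certain, and the rule does not say which variable survives it. The area factor that the trial intended to balance may therefore be missing from the model. The adolescent / transgender woman / adult man subgroup is not a candidate as such: gender does not separate adolescent from adult men, and a linear age term does so only in part.

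Prior PrEP use is a plausible predictor of starting PrEP again. It is measured before randomization but is not named for the primary model.

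**Working it through.** **Inputs.** From Sample Size: 20% v 40% uptake, alpha .05, power .80, 80 per group after attrition, 96 enrolled. From Objective 1: ten candidates, P<.15, r>0.50. Assumed: two-sided alpha; location means study area; four race/ethnicity groups; prior PrEP use with 30% prevalence and an odds ratio of 2 or 4.

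**1. The plan's own sample size.** Two-sided formulas for 20% v 40% give 82 (pooled), 79 (unpooled) and 81 (arcsine) per group. At 80 per group, power is 79.4%, and 80/(160/192) = 96. The stated figures reproduce.

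**2. Events.** 80 × 0.20 + 80 × 0.40 = 16 + 32 = 48. With the 229 recruited and the same retention, 229 × 160/192 ≈ 191 participants, and 191 × 0.30 ≈ 57 events.

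**3. Chance entry.** With ten independent null candidates, 10 × 0.15 = 1.5 are expected to pass. The chance of at least one is 1 − 0.85^10 = 80%. If state and location are removed first, eight remain: 1 − 0.85^8 = 73%.

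**4. State and study area.** For an area with share p inside a state with share s, r = sqrt[p(1 − s) / (s(1 − p))].
- Four equal areas (p = 0.25, s = 0.5): sqrt(0.125/0.375) = 0.577. The sign is positive for areas in the indicated state and negative for the others.
- Any split: take the larger area of the smaller state, so p ≥ s/2 and s ≤ 0.5. Then r ≥ sqrt[(1 − s)/(2 − s)] ≥ sqrt(0.5/1.5) = 0.577.

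In absolute value the threshold is always crossed. Under the equal split it is crossed for state and all four area indicators.

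**5. Cost of screening.** Logistic simulation with N = 160, marginal rates 20% v 40%, age and race/ethnicity always in, twelve null binary candidates screened at P<.15 (two more than the named ten), Wald test, 6,000 null and 3,000 alternative replicates:

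| | Screened | Fixed, no candidates |
|---|---|---|
| Type I error | 5.0% | 4.9% |
| Power | 78.4% | 79.5% |

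The power difference is 1.1 points.

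**6. Adding prior PrEP use.** At odds ratio 4, power rises from 79.2% (screened, without prior use) to 83.9% (age, race/ethnicity and prior use fixed), a gain of 4.7 points. A separate run of 2,500 replicates gave 77.2% to 81.6%, or 4.4 points. At odds ratio 2 the total gain is about 1 to 2 points.

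**7. Precision and model size.** At odds ratio 4, the mean standard error of the log odds ratio goes from 0.386 (screened) to 0.417 (fixed set). The ratio is 0.417/0.386 = 1.08, so the interval is about 8% wider on the log scale. The fixed set has 1 (arm) + 1 (age) + 3 (race/ethnicity) + 2 (subgroup) + 3 (area) + 1 (prior use) = 11 parameters, or 48/11 = 4.4 events each. The screened model averages 5 + 1.5 = 6.5 parameters if each candidate takes one, or 48/6.5 = 7.4 events each.

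**The case against.** The strongest reply is that little is lost. The candidates and threshold are stated in advance, type I error holds, screening costs about one point of power, and a more detailed analysis plan is promised before final analysis. All of this is correct. It limits the size of the point but does not remove it, because the article already commits to the screening and exclusion rules.

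The correlation rule may also be loose wording for dropping one of a redundant pair. That is a fair reading. Even so, the survivor must pass P<.15, so geography is still not assured. The rule is written as r, not |r|: applied with sign under the equal split, it removes state and two area indicators and leaves two. That the rule certainly deletes geography is therefore more than the text supports.

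Some stronger readings are tempting but not supported:
- *Adjustment would narrow the interval.* In logistic regression it does the opposite. The power gain comes from a larger conditional odds ratio.
- *Area was a stratification factor.* The article states an intention of equal allocation and names no stratified scheme.
- *Prior PrEP use is the best predictor available.* The documents do not show this. They list it as a potential moderator, and the wording that introduces the candidates may leave the list open.

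The sparse-data objection also stands: the proposed set has fewer events per parameter than the screened model. In the same simulation, forcing in all twelve null candidates took type I error to 6.0%, or 6.5% with prior use at odds ratio 4 and left out. The fixed set should therefore stay short.

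**Conclusion.** The point holds as a matter of pre-specification, with a modest effect on power. Ten candidates enter or leave on the outcome data, the correlation rule does not say what happens to state and study area, and prior PrEP use is not named. Validity of the test is not at stake, because screening does not materially inflate type I error.

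The power cost is about 1 point from screening. The total is about 1 to 2 points if prior use has an odds ratio of 2 and about 4 to 5 points if it is 4. Both totals rest on an assumed 30% prevalence and on assumed odds ratios. The 80% chance of a null covariate entering assumes ten independent null candidates.

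A minor side point concerns the Data Analysis overview, where "The groups will be considered not equivalent at baseline if a given variable differs significantly" (P<.05). Five independent tests of properly randomized arms would give at least one false label with probability 1 − 0.95^5 = 23%. A reader might infer that these tests also feed covariate selection. The text does not tie any covariate choice to them.

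**What to change.** Before outcomes are examined, replace the P<.15 screen and the r>0.50 rule with one fixed set: arm, age, race and ethnicity, subgroup (adolescent / transgender woman / adult man), study area, and prior PrEP use. Drop state as redundant. Collapse sparse categories by a rule written without sight of outcomes. Use the same set for Objective 3. The baseline significance tests can be dropped at the same time in favour of a descriptive table.

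The cost is wording in the analysis plan, since every variable is already collected at baseline. State the downside there too: roughly 11 parameters on about 48 expected events, and a slightly larger standard error for the adjusted log odds ratio. The return is a model known in advance and some power.
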